##### Process outcomes

The process outcomes are: knowledge of effective contraception; perceived norms and personal agency in relation to using and communicating with partners about contraception; intention to use effective contraception and intervention dose received.

### Data collection

Data will be collected at baseline and at 4 months post randomisation using questionnaires, which we tested for face validity with the target group. We asked people to comment on the length of the questionnaires, the comprehensibility of the questions, the meaning of the scales and suggestions for improvement. All data will be entered onto the trial database and randomisation system, which is on LSHTM’s secure server. At both time points, participants can either fill out a paper-based version of the questionnaire at the recruitment site, provide the data over the phone with research staff or enter data directly onto the online system, according to their preference. If participants provide their questionnaire data by paper or over the phone, research staff will enter this data onto the system.

### Baseline data collected

At baseline we will measure the primary outcome and collect the following personal and demographic data: full name; mobile phone number; email address; date of birth; marital status; number of children; residence; occupation; education level; current pregnancy intention; current method; how they heard about and enrolled in the study and the time that they prefer to receive the messages (see Additional file 1).

### Follow-up data collected

At 4 months, we will measure the primary, secondary and process outcomes and collect the following data: if participants report using an effective method, where they obtained it; current pregnancy intention; whether they knew someone else that took part in the study and, if so, if they read each other’s messages (contamination); if they have experienced physical violence since being in the study and if anything good or bad happened as a result of receiving the messages (see Additional file 2). Staff unaware of partcipants’ allocation will contact participants by phone to collect the follow-up data (participants can also complete the questionnaire online or attend the service). For participants who report use of effective contraception at follow-up, local research staff will attempt to locate the service records to objectively verify use.

### Methods to improve the quality of data collection

Closer to the start of follow-up, we will conduct a ‘follow-up refresher’ with staff who will collect follow-up data over the phone. This training will re-emphasise how to collect the follow-up data in a neutral, standardised way. Staff will also be given a suggested script and guidelines to follow when gathering the data.

### Methods to maximize follow-up response

The pre-trial training also included training in follow-up procedures. It emphasised the importance of ensuring that participants understand that participation involves completing a 4-month questionnaire and to potentially receiving daily messages about contraception for 4 months. The control messages, also sent to participants allocated to the intervention, are an effort to keep participants engaged. Staff will contact non-responders up to three times for their follow-up data. Follow-up will end 6 months after the last participant has been randomised or after staff have attempted to contact all non-responders three times, whichever comes first.

See Fig. 2 for the schedule of enrolment, interventions and assessments.

**Fig. 2 Fig2:**
[figure not shown]
Schedule of enrolment, interventions and assessments. *Plus: if participants report using an effective method, where they obtained it; current pregnancy intention; whether they knew someone else that took part in the study and, if so, if they read each other’s messages (contamination); if they have experienced physical violence since being in the study and if anything good or bad happened as a result of receiving the messages

### Allocation and protecting against bias

Randomisation will occur immediately after baseline data is submitted on the trial database and randomisation system. Participants will receive the first message the day after they install the app. The allocation sequence is generated by the remote, computer-based randomisation software, ensuring that investigators are unaware of allocation before participants are randomised. Due to the nature of the intervention, participants will be aware of the allocation soon after they start receiving the messages. Local research staff collecting outcome data will not be aware of allocation unless this is revealed to them by the participant. Researchers who analyse the data will be masked to treatment allocation.

### Intervention delivery

After randomisation, the trial database and randomisation system will send the local SMS platform the following information: allocation, time slot (participants can choose to receive messages from 10:00 to 13:59, 14:00 to 18:59, or both), mobile phone number and marital status. The platform will send the intervention or control messages. Messages sent will be recorded by the local platform and will be monitored.

### Sample size

The trial is powered to detect an increase in acceptability of effective contraception. Four hundred and fifty-four participants will allow for 90% power to detect a 15% absolute increase in acceptability, assuming 50% acceptability in the control group (i.e. 50% in the control vs. 65% in the intervention, corresponding to an odds ratio of 1.86). The sample size was calculated using the statistical software Stata 15.0 (syntax: power twoproportions .50 .65, test(chi2) power(0.9)) [68]. A 50% acceptability baseline is used in the absence of published data on acceptability in this context. If the actual baseline acceptability is higher or lower than 50%, the trial is still sufficiently powered to detect an absolute difference of 15%. For example, if the proportion in the control arm is 75%, there will be 90% power to detect an absolute difference of 12% (corresponding to 87% acceptability in the intervention group and an odds ratio of 2.23). Allowing for 20% loss to follow-up, 570 people will be randomised.

### Data management

We did not convene a Data Monitoring and Ethics Committee as the intervention provides support and is unlikely to produce adverse effects. However, we have convened a Trial Steering Committee and they have agreed to take on the monitoring of ethical aspects of the trial. The trial sponsor may audit the trial according to their own risk assessment and schedule.

Personal details entered onto the trial database and randomisation system will be stored on LSHTM’s secure server. Personally identifiable information exported from the database will be stored separately from anonymised research data on an LSHTM computer. Participant mobile phone numbers, but no other personal details, will be stored in the local platform that sends out the text messages. Signed paper Consent Forms and questionnaires will be kept in a data enclave at PFPPA. All data arising from the study will be kept confidential and is only accessible to researchers directly involved in it. Personally identifiable data will not be kept longer than necessary and will be deleted within 3 months following study completion. We will retain primary research data for 10 years following study completion.

### Analyses

#### General statistical considerations

The analysis of the data will follow the plan specified below. There will be no interim analyses and, therefore, no stopping rules. All analyses will be according to randomised arm and only participants with complete outcome data will be included in the primary analysis (a complete case analysis). All statistical tests will be two-sided. All effect estimates will be reported with a 95% confidence interval and its associated *p* value. Statistical significance will be considered at the 5% level. Analyses will be conducted using the latest version of Stata.

#### Loss to follow-up

To investigate whether loss to follow-up differs by arm, we will report this descriptively and use a﻿ chi-squared test. We will use logistic regression to compare baseline characteristics of participants who completed 4-month follow-up against participants who did not. We will report predictors of loss to follow-up and investigate whether the effect of these differs by arm by testing for an interaction.

#### Assumptions about missing data

As we are not aware of similar trials, it is not possible to investigate the pattern of missing data. The complete case analysis assumes that missing data for participants who did not complete follow-up are similar to data from participants who did complete follow-up, conditionally on baseline covariates included in the analysis model (i.e. that data is missing at random (MAR)) [69]. If participants who complete follow-up are more likely to find an effective method acceptable compared to those that are lost to follow-up, the observed proportion may overestimate acceptability [69]. European Union guidance on missing data in clinical trials highlights this limitation of MAR among others [70]. The guidance states, however, that ‘under reasonable assumptions’ the estimate of treatment effect is unlikely to be biased ‘to an important degree’. We will conduct the principal analysis under a MAR assumption (conditionally on the adjustment variables in the model), then perform sensitivity analysis under different assumptions for the missing data, as explained below.

#### Missing covariates

The database requires all items on the baseline questionnaire to be submitted to randomisation. Therefore, there will be no missing baseline covariates.

#### Principal analyses

##### Descriptive analysis

We will report a flow diagram of trial participation, as recommended in the CONSORT guidelines [71]. We will report the baseline characteristics by treatment arm. We will also explore the baseline factors associated with retention (see above).

##### Analysis of the primary outcome

The primary outcome is binary and we will compare the crude proportion reporting that at least one method is acceptable in each group. We will estimate the difference between the groups using logistic regression and will report the odds ratio along with the 95% confidence interval and its *p* value for evidence against the absence of intervention effect from the model. The primary analysis regression will be adjusted for baseline covariates likely to be associated with the outcome in order to improve the efficiency of the analysis and avoid chance imbalances [72]. These pre-specified covariates that we will adjust for are: pregnancy intention (wants to avoid/other); age (18–19/20–24 years); number of children (0/1+); highest education level completed (university/other) and acceptability of effective contraception at baseline (at least one method acceptable/no methods acceptable). We will also report the crude odds ratio between arms.

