### Intervention

The intervention is informed by the Integrated Behavioural Model [66] and consists of short mobile phone text messages providing contraceptive support delivered over 4 months. The intervention messages provide information about contraception, target beliefs identified in the development phase that influence contraceptive use (e.g. misconceptions about the side effects and health risks of contraception, belief that non-hormonal methods are better because they are not harmful to health) and aim to support young women in believing that they can influence their reproductive health. The intervention provides accurate information about contraception and contains the following behaviour change methods, adapted for delivery by mobile phone [67]: belief selection, facilitation, anticipated regret, guided practice, verbal persuasion, tailoring, cultural similarity, arguments, shifting perspective and goal setting.

The messages are tailored according to marital status, resulting in two sets of intervention messages: (1) female-married and (2) female-not married. Most of the messages in the two sets overlap, with minor tailoring so that the messages are relevant to marital status (a proxy for sexual activity). Participants allocated to the intervention group receive zero to three messages per day (113 messages for female-not married and 120 messages for female-married) for 120 days.

The message sets start with 6 days of messages (10 messages for married women and 11 for not-married women) with general information about the study, such as information about what they will receive over the next 120 days, how to stop the messages, who to contact if they change their number, how to keep the messages private and information about who to call if they feel unsafe as a result of someone reading the messages. Included in the intervention messages that the intervention recipients receive are seven control messages about the importance of their participation and reminding them to contact the project coordinator if they change their number. On days 119 and 120, the message sets include four messages that indicate that the messages have ended, provide information on how to complete the follow-up questionnaire, reassurance that the information that they provide is confidential and a final message stating that their participation is helping to determine the best ways to provide reproductive health services in Palestine.

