##### Subgroup analysis

Recognising that the trial is not powered to detect effect differences in subgroups, we will conduct exploratory subgroup analyses for the primary outcome to determine if the intervention effect varies by baseline characteristics. The pre-specified subgroups are: age (split at the median); marital status (married/not married); number of children (0/1+); residence (city/other); occupation (in education/other); highest education level completed (university/other) and pregnancy intention (wants to avoid/other). Within the pre-specified subgroups, we will assess heterogeneity of treatment effect with a test for interaction [73–77]. Interaction test *p* values will be presented but will be interpreted with caution due to the exploratory nature, the multiple tests performed and of the low power of the interaction test. We will estimate odds ratios along with 95% CIs for each subgroup without *p* values. As this is an exploratory analysis of potentially influential characteristics that are not justified a priori, we will not hypothesise effect directions.

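### The pre-specified adjustment set omits marital status, the protocol's own proxy for sexual activity: a small loss for the primary outcome, a larger one for contraceptive use

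*Protocol article*

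**What the plan says.** All references are to the protocol article.

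- **Analysis of the primary outcome.** Covariates are to be those expected to predict the outcome, to gain efficiency and to guard against chance imbalance. A closed list follows: "These pre-specified covariates that we will adjust for are: pregnancy intention (wants to avoid/other"), then age (two bands), number of children (0/1+), education (university/other) and baseline acceptability (any method/none).
- **Analysis of the secondary outcomes.** The same list is used. Only the baseline acceptability term changes, and only in the individual-method models.
- **Intervention.** "The messages are tailored according to marital status, resulting in two sets of intervention messages". Most messages are common to both sets and the tailoring is described as minor. The section speaks of "marital status (a proxy for sexual activity").
- **Baseline data collected; Missing covariates.** Marital status is recorded before randomisation, and no baseline covariate can be missing.
- **Subgroup analysis.** The listed subgroups include "marital status (married/not married"), for the primary outcome only and as exploratory.
- **Assumptions about missing data; Sensitivity analyses.** The principal complete-case analysis assumes missing at random given the model's covariates. A sensitivity analysis then adds whichever baseline variables chiefly predict loss.

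**The concern.** Marital status appears to meet the protocol's own test for a covariate, at least for outcomes that depend on sexual activity. The Background and Discussion expect many participants to be unmarried and not sexually active, or unwilling to say so. They give this as the reason why contraceptive use would yield too few events to be the primary outcome. A variable that matters that much to the design should be strongly prognostic for contraceptive use.

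The listed covariates do not stand in for it. The Background also expects newly married participants, and the 0/1+ coding of children puts those without children together with unmarried women. Baseline effective use cannot help either, because reported users are ineligible and the variable would be constant.

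Three things are at stake: precision for outcomes tied to sexual activity, protection when the arms happen to differ in the proportion married, and the credibility of missing at random if marital status predicts both response and outcome.

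**Working it through.** **1. The plan's own figure.** Inputs: "Four hundred and fifty-four participants will allow for 90% power to detect a 15% absolute increase in acceptability"; "50% in the control vs. 65% in the intervention, corresponding to an odds ratio of 1.86"; "All statistical tests will be two-sided"; "Statistical significance will be considered at the 5% level". With the pooled-variance chi-squared formula and mean proportion 0.575:

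n per arm = [1.960 × √(2 × 0.575 × 0.425) + 1.282 × √(0.50 × 0.50 + 0.65 × 0.35)]² / 0.15² = (1.370 + 0.886)² / 0.0225 ≈ 226.2, so 227 per arm and 454 in total.

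Power at 227 per arm is 0.901. Allowing for 20% loss, 454 / 0.8 = 567.5, so 568 against the stated 570. The sample size reproduces, and nothing below changes it.

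**2. Chance imbalance.** The proportion married, q, is not in the article; 20% to 50% is assumed. Under simple randomisation the SD of the arm difference is √(2q(1 − q)/227).

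| q | SD (points) | P(difference > 5 points) | P(difference > 10 points) |
|---|---|---|---|
| 0.20 | 3.8 | 18% | 0.8% |
| 0.40 | 4.6 | 28% | 3.0% |
| 0.50 | 4.7 | 29% | 3.3% |

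**3. Power with and without marital status.** Trials of 454 analysed women were simulated (1,500 replicates per primary-outcome scenario, 1,000 per contraceptive-use scenario). Assumptions: 40% married, half of the married women with children, and number of children the only other covariate. The primary outcome is 50% vs 65%; contraceptive use is assumed to be 10% vs 20%.

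| Outcome | Marital-status OR (assumed) | Power, children only | Power, plus marital status | Treatment OR, children only → plus marital status |
|---|---|---|---|---|
| Primary | 1 | 0.899 | 0.899 | 1.86 → 1.86 |
| Primary | 1.5 | 0.910 | 0.909 | 1.87 → 1.88 |
| Primary | 2 | 0.910 | 0.915 | 1.88 → 1.90 |
| Primary | 3 | 0.891 | 0.904 | 1.90 → 1.95 |
| Primary | 5 | 0.925 | 0.937 | 1.93 → 2.05 |
| Contraceptive use | 10 | 0.867 | 0.893 | 2.36 → 2.55 |
| Contraceptive use | 30 | 0.884 | 0.929 | 2.45 → 2.82 |

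The gain is −0.1 to 1.3 points for the primary outcome, and 2.6 and 4.5 points for contraceptive use. Type I error across the crude and both adjusted models was 0.036 to 0.054, so there was no inflation. A separate simulation put the primary-outcome gain at 0 to 2 points for marital-status ORs of 1.5 to 3.

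The movement in the treatment OR reflects non-collapsibility, not the removal of bias. It is a reason to settle the model in advance.

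**4. An unlucky allocation.** With no true effect, 228 per arm, half married and service uptake of 30% in married and 5% in unmarried women (all assumed), trials with a 7 to 12 point imbalance gave a mean OR of 1.08 with children in the model and 0.99 once marital status was added. The average uptake is 17.5%, so SE(log OR) ≈ √(2/(228 × 0.175 × 0.825)) = 0.25, and the shift is ln(1.08/0.99)/0.25 ≈ 0.35 SE. An imbalance of that size in a given direction occurs in about 6% of trials: P(7/4.7 < Z < 12/4.7) ≈ 0.063.

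**5. Sparse data.** In the OR 30 scenario, use p among unmarried controls solves 0.6p + 0.4 × 30p/(1 + 29p) = 0.10, which gives p ≈ 0.010. With 0.6 × 227 ≈ 136 such women, about 1.4 users are expected. Some simulated fits gave non-convergence warnings, not traced to a scenario, so the 4.5-point gain is the less secure figure. Rarer outcomes would be more exposed.

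**The case against.** The strongest reply is that the primary outcome is an attitude, chosen so that it applies to unmarried women too. No passage says that marital status predicts it, and the model already holds the baseline value of the outcome plus four other variables. This largely stands: the expected gain there is small, and the simulation probably overstates it by leaving out age, pregnancy intention and baseline acceptability, which may overlap with marital status.

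It may also be said that the Subgroup analysis section describes its variables as lacking prior justification. That remark concerns effect modification. The same list includes number of children, education and pregnancy intention, all of which the primary model adjusts for.

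On missing data, the Loss to follow-up section examines predictors of loss, and a sensitivity analysis adjusts for the main ones. That answers part of the point, but only outside the principal analysis and only if marital status emerges as a predictor. That it would do so is conjecture.

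The reply is right that an extra term is not harmless everywhere. With few or no pregnancies or abortions among unmarried women, the model could separate.

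Four stronger readings are tempting and not supported:

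- Message tailoring is not the reason to adjust. It is minor, applies only in the intervention arm, and bears on effect modification, which the interaction test addresses.
- The article does not call marital status the main determinant of service use; it says only that it is a proxy for sexual activity.
- The article's silence on stratified randomisation does not show that there was none.
- An imbalance in one trial does not make the estimator biased on average.

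**Conclusion.** The point holds as a weakness in covariate choice. It is not an error of validity: the randomised comparison is unbiased on average, type I error is not inflated, and the sample size is unaffected.

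For the primary outcome the gain is about 0 to 2 power points. The material benefit is for outcomes that depend on sexual activity, chiefly use of effective contraception, at about 2 to 5 points for marital-status ORs of 10 to 30. A further benefit is a more plausible missing-at-random condition in the principal model; this was argued, not quantified.

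The sizes rest on assumptions that the article does not supply: the proportion married, the proportion of married women with children, the strength of association with marital status, and the outcome rates for contraceptive use and service uptake.

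**What to change.** Before any look at outcomes by arm, add marital status (married/not married) to the pre-specified covariates for the primary outcome and for the contraceptive-use, individual-method acceptability and service-uptake models. For unintended pregnancy and induced abortion, include it only if the number of events allows, under a rule written down in advance, or fit a penalised (Firth) logistic model. The same fallback could be named for contraceptive use in case very few unmarried women report it.

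The cost is one extra model term and the sparse-data fallback. No new data and no additional participants are needed, since the variable is already collected, complete and dichotomised. The adjusted odds ratio will be conditional on one more variable, which is why the choice should be fixed beforehand and not made in response to an observed imbalance.
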